### 2.13. Participant Timeline

A schematic diagram of the study timeline is presented in Figure 2 and Figure 3.

### 2.14. Statistical Methods

Statistical analyses will be conducted using IBM SPSS Statistics, version 26.0 (IBM Corp., Armonk, NY, USA), under an intention-to-treat framework. A complementary per-protocol analysis will include participants achieving ≥ 70% adherence. Baseline characteristics will be summarized as mean (standard deviation) or median (interquartile range, Q1–Q3) for continuous variables, and as frequencies (%) for categorical variables. Between-group comparability at baseline will be examined using chi-square or Fisher’s exact tests for categorical variables, and one-way analysis of variance (ANOVA) or Kruskal–Wallis tests for continuous variables, according to distributional assumptions. Normality will be assessed with the Shapiro–Wilk test and by visual inspection of histograms and Q–Q plots to identify skewness, kurtosis, or outliers. When appropriate, homogeneity of variances will be verified with Levene’s test.

The primary outcome (CFQ-14 total score at 12 weeks, post-intervention) will be analyzed using linear mixed-effects models (LMMs) with fixed effects for group, time, and their interaction (group × time), and random intercepts to account for within-subject correlation. This approach accommodates repeated measures and missing data under a missing-at-random assumption [55]. Estimated marginal means with 95% confidence intervals (CIs) will be reported. Effect sizes will be presented as standardized mean differences (Cohen’s d) and partial eta squared (η^2^).

Secondary continuous outcomes (e.g., HRV, functional performance, pain, anxiety and depression, quality of life) will be analyzed using the same LMM framework. Model assumptions will be verified through residual diagnostics; if violations are detected, data transformations will be considered, or generalized LMMs with appropriate distributions (e.g., Poisson, gamma, binomial) will be applied. For categorical outcomes, between-group differences will be tested with chi-square or Fisher’s exact tests. Where adjustment for covariates is warranted (e.g., age, sex, baseline fatigue severity), logistic regression analysis will be performed, and odds ratios with their 95% CIs will be reported. No multiplicity adjustment will be applied to secondary outcomes, following common clinical trial reporting standards [56]. Pairwise post-hoc comparisons between groups and across time points will use Bonferroni correction for multiple testing. Unless otherwise specified, all tests will be two-tailed, with statistical significance set at *p* < 0.05, and results will include effect sizes and 95% CIs.

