## Abstract

**Background/Objectives:** Myalgic Encephalomyelitis/Chronic Fatigue Syndrome (ME/CFS) and Post-COVID Syndrome (PCS) are chronic conditions that share relevant pathophysiological mechanisms. Conventional rehabilitation programs have often been associated with patient dissatisfaction and frequent adverse events (AEs), highlighting the need for safer and more effective clinical approaches. This study aims to compare the effects of a telerehabilitation program based on conscious movement with those of conventional low-intensity exercise in individuals with ME/CFS or PCS. **Methods:** This is a prospective, single-blind, three-arm, parallel, superiority randomized clinical trial. A total of 147 participants (aged 18–70) with ME/CFS or PCS will be recruited and randomly assigned to one of three groups: (a) conscious movement; (b) low-intensity exercise; or c) usual care. All interventions will be delivered via telehealth over 12 weeks, with weekly 45-min sessions combining health education and individually tailored exercises. Participants will be encouraged to practice daily using the provided materials. Adherence rates and potential AEs will be recorded. The primary outcome is the total score on the 14-item Chalder Fatigue Scale at 12 weeks (post-intervention). Secondary outcomes include heart rate variability, functional performance, pain intensity and interference, mental health, interoceptive awareness, quality of life, sleep quality and fear of movement. Measurements will be collected at baseline, post-intervention, and at 3-month follow-up. **Discussion:** Recent evidence suggests that both autonomic and cognitive activity modulate immune function. Conscious movement, which integrates exercise with interoception and mindfulness-based strategies, may provide greater benefits than low-intensity exercise alone. Study limitations should be considered when interpreting the results. **Trial registration:** Registered at ClinicalTrials.gov on 15 May 2025 (NCT06978582). Protocol version 4 (29 September 2025). Ethics Committee code: 2025-0180.

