### 2.7. Sample Size

Sample size estimation considered three study groups, a one-tailed test (a larger effect size is expected in the MBE group), an α value of 0.05, a type II error (β) of 0.20 (80% power), and a precision of 6 (equivalent to a 15% change in the primary outcome, CFQ-14 total score at 12 weeks). Fatigue variance was set at 56.5 based on a previous study with a comparable population, intervention, and measurement tools [41]. Allowing for a 20% dropout rate and a design effect of 2 (due to non-probabilistic convenience sampling), a total of 147 participants (49 per group) will be required. Calculations were made using software developed by the Clinical Epidemiology and Biostatistics Unit of the Complexo Hospitalario Universitario de A Coruña, Spain [42].

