#### 2.11.1. Primary Outcome

The primary outcome is the total score of the CFQ-14 (Spanish version) at 12 weeks (post-intervention). The CFQ-14 measures perceived physical and mental fatigue over previous weeks on a 4-point Likert scale (0 = “never”, 1 = “sometimes”, 2 = “often”, 3 = “always”), total score 0 to 42, with higher scores denoting greater fatigue. The Spanish version of the CFQ-14 has demonstrated adequate reliability and validity [45]. 

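### The primary mixed model leaves out baseline CFQ-14 adjustment and relies on a random intercept alone; a baseline-adjusted model with unstructured covariance would be more precise at almost no cost

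*Protocol article*

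**What the plan says.** The endpoint is defined in section 2.11.1: "The primary outcome is the total score of the CFQ-14 (Spanish version) at 12 weeks (post-intervention"). The Abstract gives three visits: "Measurements will be collected at baseline, post-intervention, and at 3-month follow-up".

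Section 2.14 specifies the primary model. The outcome "will be analyzed using linear mixed-effects models (LMMs) with fixed effects for group, time, and their interaction", and the model has "random intercepts to account for within-subject correlation". It lists no baseline CFQ-14 covariate, no common baseline mean across arms and no other covariance structure. The same framework is carried over to the continuous secondary outcomes.

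Baseline fatigue appears as an adjustment variable only for categorical outcomes: "Where adjustment for covariates is warranted (e.g., age, sex, baseline fatigue severity), logistic regression analysis will be performed". The Additional Analyses part of section 2.14 mentions it again, but only as an exploratory moderator or predictor.

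If the model does not fit, the plan is: "Model assumptions will be verified through residual diagnostics; if violations are detected, data transformations will be considered", or a generalized mixed model is used. A different covariance structure is not among the remedies.

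The section does not say outright that baseline is a row of the outcome. Nor does it say whether the 12-week test is the difference in marginal means or the difference in change from baseline.

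**The concern.** Section 2.8 has envelopes opened only after the baseline assessments, so baseline CFQ-14 is known for every participant before randomisation. It is usually among the best predictors of the later score. With baseline as an outcome and the arm means left free at that visit, the model does not use it as a covariate. The raw 12-week contrast ignores it, so chance imbalance passes into the estimate in proportion to the correlation. The change contrast subtracts it in full, which over-corrects when the correlation is below 1. Either way, precision that has already been paid for is given up.

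Separately, a random intercept with independent residuals implies compound symmetry: the same variance at all three visits and the same correlation between every pair. If the data do not follow that pattern, the model-based standard error at 12 weeks is wrong. With dropout, the missing-at-random argument in section 2.14 also leans on this covariance being right.

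**Working it through.** **Inputs from section 2.7.** Difference 6 ("a precision of 6 (equivalent to a 15% change in the primary outcome"), variance 56.5 ("Fatigue variance was set at 56.5", so SD 7.52), one-tailed α 0.05, power 80%, dropout 20%, design effect 2, 49 per arm.

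**The plan's own figure.** n = 2 × 56.5 × (1.645 + 0.842)² / 6² = 19.41. Times 2 = 38.81. Divided by 0.80 = 48.5, rounded up to 49 per arm, or 147 in total. The figure reproduces. No baseline correlation enters it.

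**Precision.** Take complete data, equal variances and correlation ρ between baseline and 12 weeks. In units of 2σ²/n the variance is 1 for the raw 12-week difference, 2(1 − ρ) for the difference in change, and 1 − ρ² for the baseline-adjusted contrast. The saving is therefore ρ² against the first and (1 − ρ)/2 against the second. ρ is an assumption.

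| ρ | 12-week | change | adjusted | saved vs 12-week | saved vs change |
|---|---|---|---|---|---|
| 0.3 | 1 | 1.4 | 0.91 | 9% | 35% |
| 0.4 | 1 | 1.2 | 0.84 | 16% | 30% |
| 0.5 | 1 | 1.0 | 0.75 | 25% | 25% |
| 0.6 | 1 | 0.8 | 0.64 | 36% | 20% |
| 0.7 | 1 | 0.6 | 0.51 | 49% | 15% |

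At ρ = 0.5 the standard error falls by 1 − √0.75 = 13%.

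**Power for 6 points, two-sided 5%** (section 2.14 tests two-tailed), as Φ(6/SE − 1.96):

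- With the design effect: 49 × 0.8 / 2 = 19.6 per arm. Unadjusted SE = √(2 × 56.5 / 19.6) = 2.40, power 70%. Adjusted power is 78%, 82% and 88% at ρ = 0.4, 0.5 and 0.6.
- Without it: 49 × 0.8 ≈ 39 completers per arm. Unadjusted SE = √(2 × 56.5 / 39) = 1.70, power 94%. Adjusted at ρ = 0.5: SE 1.47, power 98%. With ρ = 0.3, a change contrast has 85% and the adjusted contrast 96%.

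**Covariance.** On balanced complete data, the random-intercept fit averages the three variances and the three covariances. A nominal 5% test then runs at 2{1 − Φ(1.96 × SE_model / SE_true)}. All SDs and correlations below are assumed, except the variance of 56.5; n = 39 per arm.

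- SD 5 at baseline, 7.5 later: mean variance (25 + 56.25 + 56.25)/3 = 45.83. For the 12-week contrast, model SE = √(2 × 45.83 / 39) = 1.53 and true SE = √(2 × 56.25 / 39) = 1.70. Type I error is about 7.7%.
- Same SDs with correlations 0.40 (baseline to 12 weeks), 0.35 (baseline to follow-up) and 0.70 (12 weeks to follow-up), change contrast: mean covariance (15 + 13.125 + 39.375)/3 = 22.5. Model SE = √(4 × (45.83 − 22.5) / 39) = 1.55 and true SE = √(2 × 51.25 / 39) = 1.62. About 6.1%.
- Variance 56.5 at baseline and 12 weeks, SD 9 at follow-up only: mean variance (56.5 + 56.5 + 81)/3 = 64.67. For the 12-week contrast, model SE is 1.82 against 1.70, about 3.6% (conservative).
- Compound symmetry true: the two standard errors agree, 5%.

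**The case against.** A group-by-time model with a random intercept is a standard analysis. With complete data, randomisation keeps its 12-week estimate unbiased. Covariance type and exact contrast are often left to an analysis plan, and residual diagnostics are planned. All of that is fair, and it limits the point to efficiency and robustness. It does not remove the point, because section 2.14 states the fixed and random effects explicitly, and its named remedies do not reach the covariance.

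Three stronger readings are tempting, and the protocol does not support them.

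- A reader might infer that a quarter of the precision is lost as a matter of fact. That figure is variance at an assumed ρ of 0.5. The protocol gives no correlation, and the loss depends on ρ and on which contrast is tested.
- A reader might infer that this model leaves the trial underpowered at 70%. That starting point comes from one-tailed sizing meeting two-tailed testing, with the design effect applied; it is a separate matter. Section 2.7 attributes the design effect to convenience sampling, which does not in itself inflate the variance of a randomised contrast. Without it, power is already 94%.
- A reader might infer that type I error is inflated. The protocol gives no visit-specific SDs, and the error can go either way. Section 2.3 sets no CFQ-14 entry threshold, so a compressed baseline SD is possible but not established.

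**Conclusion.** The point stands as a recommended improvement. The stated primary model omits a baseline adjustment that can only help in expectation. The saving is 9% to 49% of the variance (12-week contrast) or 35% to 15% (change contrast) for ρ from 0.3 to 0.7. In power at ρ = 0.5, that is worth 12 points with the plan's design effect and 4 points without it. The single-variance, single-correlation assumption is a risk to the standard error in either direction, and none if compound symmetry holds.

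This rests on baseline being an outcome row, which the three visits suggest but section 2.14 does not state. It also rests on complete data, equal variances for the precision table, and assumed correlations and visit SDs throughout. It is not a finding of bias or of a false statement in the protocol.

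**What to change.** Before unblinded data are seen, restate the primary model in section 2.14 in one of two ways:

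- a constrained longitudinal model with all three visits as outcomes, one common baseline mean (no arm term at baseline) and arm effects at 12 weeks and 3 months; or
- a mixed model of the two post-baseline visits with baseline CFQ-14 as a covariate.

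The first fits better with the stated aim of including everyone randomised, because a participant with only a baseline score still contributes.

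Use an unstructured covariance over visits in place of the random intercept (in SPSS MIXED, a REPEATED statement with COVTYPE(UN)). Name the MBE minus low-intensity-exercise difference at 12 weeks as the primary estimate, which matches the primary aim in the Introduction. Apply the same model to the continuous secondary outcomes.

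The cost is analysis wording and, for three visits, six covariance parameters instead of two, which 147 participants can support. No change to data collection, visits or sample size is needed.

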Health-related quality of life will be evaluated with the 36-Item Short Form Health Survey (SF-36). This tool comprises eight domain scores (physical functioning, role-physical, bodily pain, general health, vitality, social functioning, role-emotional, mental health), each transformed into a 0–100 scale (higher scores indicate better health). Physical and mental component summary scores will also be calculated. The Spanish version of the SF-36 exhibits high internal consistency across domains [47]. The severity of anxiety and depressive symptoms will be assessed using the Hospital Anxiety and Depression Scale (HADS; Spanish version). The tool includes 14 items forming two 7-item subscales (from 0 to 21 points each). Scores ≥ 8 indicate clinically relevant symptoms. The Spanish version of the HADS is reliable and widely used in clinical and research settings [48]. Sleep quality will be assessed using the Spanish version of the Pittsburgh Sleep Quality Index (PSQI). The PSQI includes 19 items grouped in 7 components, namely, subjective quality, latency, duration, habitual efficiency, disturbances, medication use, daytime dysfunction, each scored from 0 to 3. The global score ranges from 0 to 21, with values >5 indicating clinically significant sleep problems. The Spanish version of the PSQI shows good validity and internal consistency [49].

Remote assessment of functional performance has been shown to be both feasible and reliable when delivered under standardized protocols and real-time supervision [50]. The study will follow international recommendations for remote physical performance testing [50]. Before assessment, participants will receive clear instructions to prepare a well-lit space and position the camera to provide a full-body lateral view. Each test will be demonstrated in advance, and corrective feedback will be provided as needed to ensure proper execution. 

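### Categorical outcomes default to an unadjusted chi-square or Fisher test, and covariate adjustment has no stated trigger or fixed covariate list

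*Protocol article*

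**What the plan says.** All of this is in the protocol article, section 2.14, unless noted.

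- **Default test:** "For categorical outcomes, between-group differences will be tested with chi-square or Fisher’s exact tests".
- **Adjustment:** "Where adjustment for covariates is warranted (e.g., age, sex, baseline fatigue severity), logistic regression analysis will be performed", with odds ratios and 95% confidence intervals. The text gives no criterion for when this applies and does not say which of the two results is the main one.
- **Continuous outcomes:** these get a linear mixed model, partly because "This approach accommodates repeated measures and missing data under a missing-at-random assumption". Binomial mixed models are mentioned, but only as a remedy when the assumptions of the linear model fail.
- **Baseline:** "Between-group comparability at baseline will be examined using chi-square or Fisher’s exact tests for categorical variables", with ANOVA or Kruskal–Wallis tests for continuous variables.
- **Visits (Abstract):** "Measurements will be collected at baseline, post-intervention, and at 3-month follow-up".
- **Missing data (Additional Analyses):** multiple imputation is a sensitivity analysis, used if missingness is substantial. That threshold is not defined.

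**The concern.** A chi-square or Fisher test compares raw proportions and uses nothing known about participants before randomisation. This trial collects strong candidate predictors, including baseline fatigue, age, sex and baseline scores on every scale. Section 2.8 has the allocation envelopes opened only after baseline assessment, so these covariates should exist for everyone randomised. Leaving them out costs power for no saving.

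The second issue is discretion. With a default test, an optional adjusted model and no rule between them, each categorical outcome can yield two p-values. If the choice is made after both are visible, the stated 0.05 level no longer describes the procedure.

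A one-visit test also uses only participants with an outcome at that visit, whereas the mixed model was chosen for continuous outcomes because it uses partial follow-up.

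**Working it through.** **The plan's own figure.** The article gives no power figure for categorical outcomes. Its sample size for the primary outcome (section 2.7) supplies the arm size. Inputs are variance 56.5, difference 6, one-sided α 0.05, power 80%, design effect 2 and dropout 20%.

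- n = 2 × 56.5 × (1.645 + 0.842)² / 6² = 19.41 per group
- 19.41 × 2 / 0.80 = 48.52, rounded up to 49; 49 × 3 = 147. This reproduces the plan.
- With 20% dropout, 49 × 0.80 = 39.2, so about 39 per arm have an outcome.

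**Assumptions, because the article gives no event rates or correlations.** Two arms of 39 are compared. The outcome is a latent normal score cut at the control median. The true shift is 0.6 SD, and the baseline-to-outcome correlation is 0.3, 0.5 or 0.7. The shift lies between the meta-analytic effect of 0.44 cited in the Introduction and the effect implied by section 2.7, 6/√56.5 = 0.80.

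**Hand check of the default test.** The proportions are 0.50 and Φ(−0.6) = 0.274, a difference of 0.226; the mean proportion is 0.387.

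- Standard error under the null = √(2 × 0.387 × 0.613 / 39) = 0.110
- Standard error under the alternative = √((0.250 + 0.199) / 39) = 0.107
- Power = Φ((0.2257 − 1.96 × 0.1103) / 0.1073) = Φ(0.09) = 54%

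**Simulation, 4,000 trials per setting, two-sided 0.05.** The adjusted model is logistic regression on arm and baseline score.

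| Correlation | Power, chi-square | Power, adjusted | Gain (points) | Type I, chi-square | Type I, adjusted | Type I, smaller p |
|---|---|---|---|---|---|---|
| 0.3 | 54.8% | 57.6% | 2.8 | 5.2% | 5.6% | 6.4% |
| 0.5 | 55.3% | 62.6% | 7.3 | 4.4% | 4.6% | 6.4% |
| 0.7 | 54.4% | 71.0% | 16.6 | 5.6% | 5.1% | 8.2% |

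The Monte Carlo standard error is √(0.05 × 0.95 / 4000) = 0.3 points for type I error and √(0.55 × 0.45 / 4000) = 0.8 points for power. A separate repeat gave 54% for chi-square against 57%, 62% and 71% adjusted.

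**Adjusting only when a baseline test has p < 0.05.** This rule fires in about 5% of trials. Power is 55.0%, 55.6% and 55.2%, with type I error of 4.2% to 5.3%. It does no harm to the error rate but recovers almost none of the lost power.

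**Missing outcomes, separately.** For assumed rates of 60% against 40%, chi-square power falls from 51% at 49 per arm to 42% at 39. For 60% against 30%, it falls from 86% to 77%.

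**The case against.** The strongest reply is that this is detail for an analysis plan that is not shown, and that chi-square with supporting logistic regression is a valid analysis. Both parts carry weight. Each method alone holds its level, and a SAP may fix the covariates. However, the article does not leave the method open: it states an unadjusted default and a conditional adjustment. That stated choice can be improved with data already being collected.

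Several stronger readings are tempting, but the document does not support them:

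- **Baseline p-values decide the covariates.** Section 2.14 plans the baseline tests but never links them to adjustment, and the covariates it lists are plausible prognostic factors. The tests are uninformative in their own right, since randomisation makes their null hypothesis true.
- **The HADS cut-off is a planned binary endpoint.** Section 2.11.2 says "Scores ≥ 8 indicate clinically relevant symptoms", but that describes how to read the scale. Section 2.14 puts anxiety and depression among the continuous outcomes. The PSQI threshold is likewise given only for interpretation.
- **Participants with missing visits are simply dropped.** A one-visit test implies this but the article does not say it, and the conditional multiple imputation is not confined to continuous outcomes.
- **Baseline data are thrown away.** This is true only of the default test; baseline fatigue severity is listed as a possible covariate.
- **The smaller p-value will be reported.** The article plans no such thing. The 6–8% is what the open wording would permit.

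Two further limits stand. Adverse events, PEM episodes during the trial and attendance are natural categorical outcomes but have no baseline value of their own. The simulation tests single-visit logistic regression, so it does not measure any gain from a mixed model.

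**Conclusion.** The point holds within a narrow scope. The stated default for categorical outcomes is inefficient, and the condition for adjusting is open. The estimated cost is about 3 to 17 points of power, depending on how strongly the covariates predict the outcome. If the better p-value were chosen, type I error would be about 6–8% instead of 5%.

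These figures rest on the assumed 39 per arm, 0.6 SD shift, cut at the control median and correlations of 0.3 to 0.7. For outcomes with no baseline value of their own, the covariates may predict less well, and the low end of the range is then the better guide.

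The primary outcome and the continuous secondary outcomes, HADS included, are not touched, and no categorical efficacy endpoint is named. The change is worth making because it is nearly free, not because the trial's main conclusion is at risk.

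**What to change.** In section 2.14, or in the SAP before unblinding:

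1. For each non-rare binary outcome, make one logistic model the main analysis. Include group, age, sex and baseline fatigue severity, plus the outcome's own baseline value where one exists. Remove the conditional wording.
2. Where the outcome is measured at repeated visits, use the binomial mixed model the plan already mentions (group, visit, group × visit, random intercept, the same covariates). A participant who misses one follow-up visit then still contributes the other.
3. Keep Fisher's exact test for rare events.
4. Describe baseline by summary statistics only, and state that baseline p-values will not be used to choose covariates.

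The cost is a few sentences and slightly more analysis work, with no new data and no change to the sample size. The downside is that odds ratios become conditional on the covariates, so the raw proportions by arm should be shown beside them. The article reports that recruitment was still under way (section 5), which leaves time to settle this before analysis.

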### 2.8. Allocation to Interventions

Eligible participants will be randomly assigned to one of three arms: (1) MBE, (2) conventional low-intensity exercise, or (3) usual care. Recruitment will occur in three waves (*n* = 50, 49, and 48), each randomized independently to ensure a 1:1:1 ratio (16–17 participants per arm per wave). Randomization sequences will be computer-generated in R (with seed set for reproducibility) using stratified lists to minimize imbalance across groups. The R script for the stratified randomization is in Supplementary File S1. Allocation concealment will be ensured with sequentially numbered, opaque, sealed envelopes, prepared by an independent collaborator not involved in recruitment or assessment. Envelopes will be opened only after consent and completion of baseline assessments.

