## 4. Conclusions

This trial aims to examine the effects of a 12-week mindful exercise telerehabilitation program compared to conventional exercise and usual care in individuals with ME/CFS and PCS. Beyond testing feasibility and clinical outcomes, this study seeks to elucidate whether an interoceptive, symptom-titrated approach can support safer and more sustainable physical activity engagement.

Findings from this trial may help refine personalized rehabilitation strategies and inform the integration of telerehabilitation into routine clinical pathways for ME/CFS and PCS. By providing a structured, evidence-based model of remote delivery, the protocol could serve as a foundation for future multicenter or cross-national collaborations and guide health policy decisions toward broader access to individualized, home-based rehabilitation options.

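### Bonferroni for the pairwise comparisons is valid but needlessly conservative: Holm, or with three arms a Shaffer-type step within a visit, holds the same 5% and rejects more

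*Protocol article*

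**What the plan says.** Section 2.8 sets up three arms in equal ratio: "Eligible participants will be randomly assigned to one of three arms". Section 2.14 analyses the primary and the continuous secondary outcomes in one mixed-model framework and then gives three rules in close succession.

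- On secondary outcomes: "No multiplicity adjustment will be applied to secondary outcomes".
- In the next sentence, on pairs: "Pairwise post-hoc comparisons between groups and across time points will use Bonferroni correction".
- On reporting: "results will include effect sizes and 95% CIs", with two-tailed tests at 5% unless otherwise specified.

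The Bonferroni sentence is not limited to the primary outcome, and the number of comparisons in its family is not given. The Introduction states one primary aim, MBE against low-intensity exercise on CFQ-14 after 12 weeks. The Conclusions describe the trial's comparison as "compared to conventional exercise and usual care in individuals with ME/CFS and PCS".

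**The concern.** The tests at issue are the pairwise ones other than the primary contrast: each active arm against usual care, the pairs at the 3-month follow-up, and the pairs on secondary outcomes. Bonferroni tests every pair at 0.05/3, or lower if visits are pooled, however strong the evidence on the other pairs. Stepwise procedures relax the level once a first hypothesis has been rejected and still hold 5%. If they are available at no cost in error control, a fixed 0.05/3 gives away power on the usual-care contrasts, which tell the reader whether either programme does anything at all.

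The two adjacent sentences also leave it open which rule governs a pairwise test on a secondary outcome.

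**Working it through.** **1. The protocol's own sample size.** Inputs from section 2.7: difference 6, variance 56.5, one-tailed 0.05, 80% power, design effect 2, dropout 20%.

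n = 2 × 56.5 × (1.645 + 0.842)² / 6² = 19.41 per arm; × 2 / 0.8 = 48.52, rounded up to 49; × 3 = 147. The stated total reproduces and contains no Bonferroni allowance. Analysable per arm: 49 × 0.8 = 39.2, about 39. If the design effect is also taken as a loss of information: 39.2 / 2 = 19.6, about 20 effective.

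**2. Levels for three pairs at one visit.**

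| Step | Bonferroni | Holm | Shaffer-type |
|---|---|---|---|
| Smallest p | 0.0167 | 0.0167 | 0.0167 |
| Second | 0.0167 | 0.025 | 0.05 |
| Largest | 0.0167 | 0.05 | 0.05 |

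The first step is the same and the later ones are never stricter. Both stepwise rules therefore reject everything Bonferroni rejects.

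**3. Why the Shaffer-type step holds 5% at one visit.** If A = B and B = C, then A = C, so the number of truly equal pairs is 3, 1 or 0, never 2.

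- Three equal: an error requires the smallest p below 0.05/3, which has probability at most 5%.
- One equal: that pair can be rejected only if its own p is below 0.05, so at most 5%.
- None equal: no false rejection is possible.

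Simulated family-wise error is 4.3% for both Bonferroni and Shaffer with all arms equal. With one pair equal and the third arm far away it is 1.7% for Bonferroni and 5.0% for Shaffer, within simulation error.

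**4. Power.** Three equal arms, SD = √56.5 = 7.52, pooled variance, two-sided t tests, family of three pairs at one visit. Shifts are MBE / exercise / usual care in CFQ-14 points. They are assumptions; the protocol gives none against usual care.

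| Shifts | Contrast | n per arm | Bonferroni | Holm | Shaffer |
|---|---|---|---|---|---|
| −4/−4/0 | each active arm vs usual care | 39 | 47% | 50% | 54% |
| −6/−3/0 | exercise vs usual care | 39 | 26% | 33% | 40% |
| −6/−3/0 | exercise vs usual care | 20 effective | 12% | 15% | 21% |
| −6/−3/0 | MBE vs usual care | 39 | 86% | between the two | 87% |

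Hand check of the second row: SE = √(2 × 56.5 / 39) = 1.70; 3 / 1.70 = 1.76; the normal critical value at 0.05/3 two-sided is 2.39; Φ(1.76 − 2.39) = Φ(−0.63) = 26%.

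**5. Across visits.** The protocol's sentence also covers time points. With two post-baseline visits and all arms equal, Bonferroni over three pairs at each visit separately gives 8.6%, 8.0% and 7.0% overall error at assumed visit correlations of 0, 0.5 and 0.8. Over all six tests it gives 4.5%, 4.2% and 3.8%. The Shaffer step used at each visit separately can reach 1 − 0.95² = 9.75% over two independent visits. Holm over the six tests keeps 5%. Its levels run from 0.05/6 = 0.0083 up to 0.05, so it again never rejects less than Bonferroni on those six. The size of that gain depends on the unknown correlation between visits; the figures in step 4 are for one visit.

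**6. Test and interval.** If the 95% intervals are unadjusted, they exclude zero exactly when raw p is below 0.05. For exercise vs usual care at −6/−3/0 with 39 per arm, that happens in 41.5% of trials. The share where the interval excludes zero but the adjusted test is not significant is about 41.5 − 26 = 15.5 points with Bonferroni, 41.5 − 33 = 8.5 with Holm and 41.5 − 40 = 1.5 with Shaffer. At −4/−4/0 raw power is about Φ(4/1.70 − 1.96) = 65%, so the shares are roughly 18, 15 and 11 points.

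**The case against.** The strongest reply is that nothing in the rule is statistically wrong. Bonferroni controls error, the comparisons are called post hoc, the protocol states no separate hypothesis for the usual-care pairs, and choosing among valid procedures is partly taste. It also offers matching simultaneous confidence intervals, and the plan promises intervals with every result. The family may be defined in an analysis plan that is not shown. All of this stands, and it limits the point to lost efficiency. It does not remove it, because the stepwise rules reject a superset at the same error level and cost only wording.

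A reader might infer that the adjacent sentences contradict each other. They do not have to: no correction across secondary outcomes, and Bonferroni among the pairs and visits within one outcome, is a natural joint reading. That is an ambiguity to tidy, not a conflict.

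A reader might also prefer a larger gain: a 2-df test of the arms at each visit, then each pair at 5%, reaches 58% at −4/−4/0. That rule should not be adopted as a simple replacement. It drops the time-point part of the protocol's sentence (8.0% to 9.8% error over two visits with all arms equal). It can miss a pair Bonferroni would reject (up to 0.5% per pair). And when the overall test fails it leaves ordinary intervals that exclude zero, in about 7% of trials for each usual-care contrast at that setting.

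Finally, the gain is uneven. At −6/−3/0 MBE vs usual care moves by only about one point.

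**Conclusion.** The point holds as an inexpensive improvement. Bonferroni is valid, but Holm on the same family is never less powerful, and the three-arm Shaffer step is better still if error is to be held within a visit only. In the settings tried with 39 per arm, the usual-care contrasts with room to improve gain 3 to 7 percentage points with Holm and 7 to 14 with Shaffer. With about 20 effective per arm, exercise vs usual care gains 3 and 9.

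These sizes rest on assumed shifts, on the CFQ-14 variance of 56.5, and on t tests standing in for the mixed-model contrasts. They do not transfer to secondary outcomes with other variances, although the ordering of the methods does.

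The documents do not support saying that error is inflated, that the power is given up for nothing (matching simultaneous intervals are a real return), or that section 2.14 contradicts itself. The primary contrast is outside this point.

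**What to change.** Replace the Bonferroni sentence in section 2.14 with wording such as:

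> For each outcome, pairwise comparisons between arms at the post-baseline visits form one family and are adjusted by Holm's method. No correction is made across secondary outcomes. Pairwise 95% confidence intervals are unadjusted and are labelled so. The primary contrast, MBE vs low-intensity exercise on CFQ-14 at 12 weeks, is not part of these families.

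If the sponsor prefers each visit to be its own family, use the three-arm Shaffer step at that visit and state that error is then controlled per visit only. If changes over time within an arm are also meant to be tested, say whether they belong to the family; Holm accommodates any number of tests.

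The cost is wording, before analysis. The downside is that there are no matching simultaneous intervals, so an unadjusted interval will sometimes exclude zero when the adjusted test is not significant (step 6 above gives the size). Labelling the intervals makes this visible. If simultaneous intervals matter more to the sponsor than power, keeping Bonferroni with explicitly adjusted intervals and a stated family is a defensible alternative.
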